#### Absolute stopping criteria:

The exercise stress test will be stopped and the participant will be excluded if any of the following occur:

- drop in systolic BP of >10 mm Hg from baseline BP despite an increase in workload when accompanied by other signs of ischemia.
- Moderately/ severe angina (defined as 3 on the ACSM standardised rating scale),
- increasing nervous system symptoms (e.g. ataxia, dizziness, or near syncope),
- signs of poor perfusion (cyanosis or pallor),
- subject desire to stop,
- sustained ventricular tachycardia, ST elevation (+1.0 mm) in leads without diagnostic Q waves (other than V1 or aVR).

We will also use the following relative criteria. If the participant meets one of the relative criteria below, we will consult the treating clinician to determine if the participant is medically sound to be included in the trial and perform the exercise session at the planned intensity.

- drop in systolic BP of >10 mm Hg from baseline BP despite an increase in workload in absence of other signs of ischemia
- ST or QRS changes such as excessive ST depression (>2 mm horizontal or down-sloping ST-segment depression) or marked axis shift
- Arrhythmias other than sustained ventricular tachycardia, including multi focal PVCs, triplets of PVCs, supraventricular tachycardia, heart block, or brady-arrhythmias
- Fatigue, shortness of breath, wheezing, leg cramps or claudication
- Development of bundle-branch block or intra-ventricular conduction delay that cannot be distinguished from ventricular tachycardia
- Increasing chest pain

Alongside the physiological recordings, the Borg Rating of Perceived Exertion (RPE) [38] will be used in the Fitness test as a subjective reporting measure of exercise difficulty, in order to help moderate activity intensity.

At the completion of the study, participants who request information regarding their Fitness test progress will be provided with a letter indicating whether they are performing at, below, or above the average for their age range, compared to people who have not experienced a stroke. This letter will also direct participants to speak to their local doctor about possible referral to an Exercise Physiologist or Physiotherapist, should they express interest in improving their physical fitness subsequent to participation in the study.

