### **c. RANDOMISATION**

After the first time-point assessments, participants will be randomly allocated into one of two exercise groups using a computer generated schedule with permuted blocks of various sizes. This will be part of the electronic case report form (ECRF) hosted at a secure server at the Florey and compliant with Good Clinical Practice (GCP) guidelines for clinical trials. The randomisation will be stratified by baseline function (modified Rankin Scale score, grouped into mRS 0-1, 2-3) and baseline total brain volume (low, high).

Participants will be aware of their group allocation based on the exercise programme they are administered. Investigators who are blind to participant group will conduct cognitive testing, MRI analysis, and cardiovascular testing.

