## **VIII. Fitness test of aerobic capacity – VO2 peak graded exercise test (GXT)**

Aerobic capacity will be repeatedly assessed at each study visit via a submaximal, incremental exercise test. At the initial Baseline visit, information from the GXT will also be used to create each participant's graduated exercise programme.

All participants will undergo a  $VO_{2peak}$  graded exercise stress test to determine exercise capacity using a metabolic cart (the Oxycon mobile™, CareFusion). A submaximal GXT will be conducted at each of the three study visits to monitor the change in aerobic capacity. The GXT will take place at the Florey, Melbourne Brain Centre, Austin campus, or in the AIMSS facility at Western Health, under the supervision of a trained exercise professional. This person will not be involved with the exercise training as they are not blinded to participant status.

The following parameters will be recorded during the test:  $VO_{2peak}$  (volume oxygen uptake in ml/kg/min), Heart Rate (HR), Heart Rate Reserve (HRR, subtracting resting heart rate from the maximum heart rate measured during an exercise test), Oxygen Saturation, and Respiratory Rate (RR, number of breaths per minute). These parameters will enable us to derive  $VO_{2peak}$  as an estimate of aerobic exercise capacity. Blood pressure and ECG recordings will be monitored as markers of participant well-being.

A total body recumbent stepper will be used to perform the GXT, as outlined by Billinger [32]. This submaximal GXT protocol has been shown to be a valid measurement of  $VO_{2peak}$  [35], and prescribing cardiorespiratory exercise based on  $VO_{2peak}$  values is safe in a subacute stroke population with mild to severe post-stroke deficits [36].

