Participants will be asked to maintain a step rate of 80 steps per minute on a recumbent stepper. The test will start at a power output of 15 watts and will be increased every 2 minutes by an amount that is predefined in the protocol (see Box 1, based on Billinger 2008). The amount will increase until completion or until volitional fatigue, or 85% of age predicted heart rate was achieved ( $0.85[220 - \text{age}]$ ). HR will be recorded every 10 seconds at the end of the second and third minute. If the change in HR between the second and the third minute is less than 5 bpm then the resistance will be moved to the next stage. If it is over 5 bpm an additional minute will be performed at the same stage to make sure steady state will be reached.  $VO_{2peak}$  will be determined by imputing HR and workload into the following equation  $VO_{2peak} \text{ (ml.kg.min)} = 125.707 + (-0.476)(\text{age}) + (7.686)(\text{sex } [0 = \text{female}; 1 = \text{male}]) + (-0.451)(\text{weight in Kg}) + (0.179)(\text{Watts end\_submax}) + (-0.415)(\text{HREnd\_submax})$ .

| Stage  | Resistance (W) | Stepping cadence
(steps x min) | Duration (min) |
|--------|----------------|-----------------------------------|----------------|
| Load 1 | 25             | 80                                | 2              |
| Load 2 | 40             | 80                                | 2              |
| Load 3 | 55             | 80                                | 2              |
| Load 4 | 70             | 80                                | 2              |
| Load 5 | 85             | 80                                | 2              |
| Load 6 | 100            | 80                                | 2              |
| Load 7 | 115            | 80                                | 2              |

|        |     |    |   |
|--------|-----|----|---|
| Load 8 | 130 | 80 | 2 |
|--------|-----|----|---|

*Based on exercise protocol described in Billinger et al. [35].*

The GXT will be stopped using the safety criteria of exercise testing according to the American College of Sports Medicine (ACSM) exercise testing and prescription guidelines [37].

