1013 Participants will be excluded if the following eligibility criteria are not met during the initial  
1014 screening:

- 1015 • Significant medical co-morbidities (e.g., severe cardiac disease) and/or musculo-skeletal  
1016 injuries precluding participation in exercise intervention, or making survival for 1 year  
1017 post-stroke unlikely;
- 1018 • Pregnancy;
- 1019 • Normal exclusion criteria for MRI; e.g., implanted metal, severe claustrophobia;
- 1020 • Pre-existing dementia
- 1021 • mRS >3.\*

1022  
1023 \* In order to have a cohesive cohort for this study, we have elected not to include  
1024 participants with a premorbid diagnosis of dementia or cognitive decline.

1025                   d. CONSENT

1026 Written informed consent will be obtained from participants via a Participation Information  
1027 and Consent Form (PICF). The PICF will detail the purposes of the project, issues  
1028 surrounding confidentiality and the storage and sharing of their data, potential benefits and  
1029 risks associated with their participation, and other information required for participants to  
1030 make an informed decision about their participation.

1031 A copy of the PICF will be provided to each participant to read through (i.e., in person while  
1032 they are inpatients or via mail post-discharge), and they will be given time to consider their  
1033 participation in the study within the 2-month post-stroke timeframe. As we outlined above in  
1034 Section 6 (Recruitment Procedure), participants will be screened to ensure that they have  
1035 the cognitive capacity to provide informed consent – that is, we do not intend to ask their  
1036 spouse or next-of-kin to provide informed consent on their behalf at recruitment.

1037 For those participants who do not provide signed consent during their inpatient admission, a  
1038 reply-paid envelope will be given for them to return the Consent Form once they have made  
1039 a decision. If the Consent Form is not received from potential participants within the 2 month  
1040 post-stroke time period they will be contacted via phone by one of the study investigators to  
1041 ask if they have any further questions about the study.

1042 As detailed in Section 5d (II), some participants will be invited to take part in the study after  
1043 they have been discharged. The investigator will call the participant to discuss the study and  

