#### c. STATISTICAL METHODS TO BE UNDERTAKEN

The analysis can be considered in 3 parts, aligned with primary and secondary hypotheses:

- i. **Primary outcome and hypothesis: Comparing brain volumes between stroke participant groups:** Primary outcome will be analysed on an intention to treat basis, The difference in brain volume from baseline to 4 months will be analysed using an ANCOVA model with exercise intervention group as a factor (e.g., Physical fitness training vs. Balance training groups), with baseline brain volume and functional status as co-variants (dichotomised as mRS = 0-1, 2 and 3).
- ii. **Secondary outcome and hypotheses: Correlating brain volume with blood pressure control and incident stroke:** Secondary outcomes will be analysed using appropriate repeated measures random effect logistic regression models with dichotomised hypertension status or silent/recurrent brain infarction (as defined in methods) as dependent variables, treatment group as independent variable, and functional status dichotomized as a covariate (as above). The initial regressive analysis will examine the

differences between participants with good and poor blood pressure control, using this as a binary measure. The presence of incident subclinical stroke will also be included as a binary variable. In the regional volumetric analyses, total brain volume, regional white matter, cortical and subcortical grey matter volume changes will be modelled using this design.

- iii. **Exploratory analyses: Independent effects of exercise on blood pressure, incident stroke, diastolic cardiac indices, and aerobic capacity:** Exercise effects on end-organ function and fitness (i.e., aerobic capacity) are likely dissociable, however emphasise that this component is exploratory. For the purposes of these analyses, we define each of our end-organ metrics as: brain volume, cognitive function, incident stroke, diastolic cardiac indices, aerobic capacity (VO2max), sleep duration, onset latency, bedtime/rise time variability (minutes), and sleep efficiency (%). Exploratory analysis will be conducted using appropriate regression models to investigate the associations between BP, incident stroke, diastolic cardiac indices, aerobic capacity. In addition, mediation analyses will be conducted to explore the possible mediating role of sleep in preservation of brain volume.

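### The graded exercise test rules conflict: a voluntary stop is both a normal end of test and a ground for exclusion, and the stage rules cannot all be followed

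*Protocol*

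**What the plan says.** All of the conflicting rules stand in Protocol section 5.d.VIII.

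- **Normal end of test.** "The amount will increase until completion or until volitional fatigue, or 85% of age predicted heart rate was achieved".
- **Absolute criteria.** "The exercise stress test will be stopped and the participant will be excluded if any of the following occur". The list holds medical signs such as angina, poor perfusion and ventricular tachycardia, and also "subject desire to stop".
- **Relative criteria.** Fatigue is on this list. Meeting a relative criterion leads to a consult with the treating clinician on whether the person is "medically sound to be included in the trial and perform the exercise session at the planned intensity".
- **Visits.** "A submaximal GXT will be conducted at each of the three study visits to monitor the change in aerobic capacity". Section 5.c places randomisation after the first of these: "After the first time-point assessments, participants will be randomly allocated into one of two exercise groups".
- **Stages.** The text starts at 15 W and raises the load every 2 minutes. The table starts at 25 W (Load 1), rises by 15 W per stage to 130 W (Load 8) and gives 2 minutes per stage. Progression compares heart rate at the end of the second and third minutes: under 5 bpm of change moves the participant up, and over 5 bpm adds a minute at the same stage.

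The baseline test also sets the initial aerobic prescription (section 5.b, Exercise groups and programmes). Aerobic capacity is a secondary measure in the Synopsis, is exploratory in section 8.c, and is not on the outcome list in section 4.c.

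**The concern.** The protocol draws no line between volitional fatigue and a wish to stop. A participant who stops from tiredness has, on the text, finished a valid test, triggered a consult and met an absolute ground for exclusion. Stopping on request is plainly right; excluding the person for it is the problem. People with mRS up to 3 are eligible, and those who stop early are plausibly the less fit, so the rule could narrow the sample away from part of the population the trial means to study.

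The stage rules raise a separate difficulty. Staff cannot run a 2-minute stage and also read heart rate at minute 3, so each tester must choose which instruction to drop. The test is run at more than one location and three times per participant. If the choice differs between sessions, estimated VO2peak carries error that has nothing to do with fitness.

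**Working it through.** **1. Consequences of one event.** Take a participant at the baseline test who says they are tired and want to stop.

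| Rule in 5.d.VIII | Consequence |
|---|---|
| Volitional fatigue (end of test) | Test complete and valid |
| Fatigue (relative criterion) | Clinician consult |
| Wish to stop (absolute criterion) | Test stopped, participant excluded |

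Nothing else in the protocol says which rule prevails. The eligibility list in section 6.c does not name this ground. That section is limited to the initial screening ("Participants will be excluded if the following eligibility criteria are not met during the initial" screening), so it does not contradict the test rule, but it does not resolve the conflict either.

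**2. Which visit.** The test is done at 2, 4 and 12 months, and randomisation follows the 2-month assessments. The exclusion sentence is tied to none of these visits. The paired relative rule speaks of inclusion in the trial, which makes sense only at baseline. The likely explanation is an omitted phrase.

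**3. Start load.** The table ladder is 25, 40, 55, 70, 85, 100, 115, 130 W. Assuming the same 15 W step (40 − 25), a 15 W start gives 15, 30, 45, 60, 75, 90, 105, 120 W. The two ladders share no load.

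**4. Stage length.** The heart-rate check needs at least 3 minutes per stage, or 4 when the extra minute is used. For all eight stages:

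- 8 × 2 = 16 minutes, as the text and table state
- 8 × 3 = 24 minutes, as the heart-rate check needs
- 8 × 4 = 32 minutes, if every stage needs the extra minute

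**5. What the estimate is sensitive to.** The protocol's equation weights end-of-test heart rate at −0.415 per bpm and end-of-test load at +0.179 per W. Start load is not an input.

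- If heart rate would still rise 5 bpm in minute 3, ending the last stage at 2 minutes instead of 3 at the same load raises the estimate by 0.415 × 5 = 2.075, about 2.1 ml/kg/min.
- If the test ends on the 85% heart-rate limit, finishing one 15 W stage higher at that heart rate raises it by 0.179 × 15 = 2.685, about 2.7 ml/kg/min.

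These figures are conditional illustrations, not expected errors. They matter only if sessions follow different readings of the rules.

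**The case against.** The strongest reply is that these are drafting slips with little reach, and much of it stands.

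- **Fatigue has a route that does not exclude.** Because it is a relative criterion, many people who stop from tiredness would in practice go to a consult. This softens the concern about losing the less fit. It does not remove it, because the absolute rule is phrased without exception.
- **The visit.** A reader might infer that the rule removes randomised participants at 4 or 12 months and so breaches the commitment "Primary outcome will be analysed on an intention to treat basis" in section 8.c. The documents do not support that. It needs two readings the text does not state: that the rule applies after randomisation, and that exclusion means leaving MRI, follow-up or analysis. The relative rule points to baseline, and section 7.c keeps data collected before a withdrawal in all analyses as its default.
- **Stage rules.** If one reading were applied throughout, both arms would be affected alike. Variation between testers is possible but not demonstrated.
- **Remedy.** The protocol bases the test on a published procedure (reference 35) that is not available here. Imposing 3-minute stages could depart from it, so the stage length should be settled against that source.
- **Entry rule.** Excluding anyone who asks to stop may be deliberate caution before home exercise supervised by video. That is a clinical judgement. A symptom check or consult, together with the physician clearance already required in section 7.a, can serve the same purpose without automatic exclusion.

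**Conclusion.** The point holds as an internal contradiction in the operative test instructions. As written, an eligible participant can be excluded for voluntarily ending a submaximal test, and the stage rules cannot all be followed. The missing visit is a minor omission.

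The effect is confined to who enters the trial, the baseline exercise prescription and the consistency of aerobic capacity. Loss before randomisation narrows the sample but does not bias the comparison between arms. A reader might go further and infer harm to the brain-volume endpoint, its power or its error rate; no such effect is shown. The number of people affected cannot be stated, because the protocol gives no stop rate. That those who stop are less fit is an assumption. Severity is minor to moderate.

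**What to change.** Replace the exclusion sentence with four statements:

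1. Any absolute criterion stops the test.
2. At the baseline test, before randomisation, a participant who meets a medical absolute criterion (every listed one except the wish to stop) is not randomised.
3. A voluntary stop ends the test at any visit and prompts a symptom check or clinician consult, but is not in itself a ground for exclusion.
4. A stop at 4 or 12 months ends that test only. Exercise is restricted if medically needed, while MRI, follow-up and intention-to-treat analysis continue.

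Have the exercise lead make the start load, stage length and heart-rate check agree with one another and with the cited test protocol, and apply them identically at every site and visit. The lead should also say how VO2peak and the prescription are set after a voluntary stop, including when the first stage is not completed.

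The cost is a wording amendment and a note to sites. Every safety stop is kept. Some fitness tests will be incomplete. If 3-minute stages are adopted, a full eight-stage test takes 24 minutes, and up to 32 with extra minutes, instead of 16. Section 5.b allots 30 to 60 minutes for the test but does not say whether set-up and recovery are included, so the longer case should be checked against that slot.

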## **IX. Physical activity monitoring**

Physical activity and energy expenditure will be monitored by an Actiwatch Spectrum Plus (Koninklijke Philips, Amsterdam, Netherlands). The Actiwatch is a small, unobtrusive electronic physical activity monitor on an adjustable wrist strap that is worn on the left wrist. If participants have left-arm paresis the monitor will be fitted to the right wrist. Participants will be asked to wear the waterproof Actiwatch 24 hours per day for 7 days. In previous studies, conducted by the current Investigators, involving the use of Actiwatches for the duration specified there have been no complaints or concerns raised by participants.

The Actiwatch will be fitted onto participants at each of the three timepoints throughout the study, after the MRI scan and cognitive testing has been completed. Following the 7 day monitoring period, participants will be asked to return the de-identified Actiwatch in a de-identified pre-paid envelope to the study investigators.

In addition, participants will be asked to keep a daily activity diary that records participant activity levels between assessment visits. Such diaries are common place as a part of general post-stroke rehabilitation programmes and this is not expected to be an inconvenience for participants.

Time spent active will be used as a co-variate for data analysis.

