### Timelines and feasibility

The 8 week intervention will commence at 2 months after stroke (see Figure 1. Experimental design and participant timeline). At the 2 month, 4 month, and 1 year post-stroke time-points,

we will capture brain images with MRI, perform ambulatory BP measurements and cognitive testing, assess aerobic capacity, fit Actiwatches, deliver the 7-day Sleep Diary and sleep questionnaire, and explain how to use the Research Food Diary app (sleep and dietary assessments to be completed at home). Blood samples will be collected at each time-point to check for concurrent changes in levels of BDNF and HbA1c. Additional blood (10ml) will be collected at the first (2 months post-stroke), second (4 months post-stroke), or third (12 months post-stroke) to test for APOE status and genetic risk. Stool samples will be collected by participants at home after each time point and they will be returned by the participant to the study site with the 24-hour BP device.

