### Participant home visits

One home visit will take place 1-week prior to the initial baseline assessment and prescription of exercise programme at the 2 month post-stroke timepoint. At the home visit, an Exercise Professional (EP) and/or Occupational Therapist (OT) will assess the safety of the area the participant will be exercising in and minimise potential risks.

Home Visit Risk Management Procedures and Guidelines will be followed as per The Florey's Occupational Health and Safety Manual Section 1 (please refer to <https://unimelbcloud.sharepoint.com/sites/florey/ohs/>).

A friend or family member will attend the initial home visit. The EP/OT will determine the level of involvement of this contact, depending on the participant's level of independent function and mobility. The emergency contact will either a) solely provide their contact details in case of emergency or b) act as a study partner and will need to be in the participant's home for each of the sessions. Study partners will sign a separate consent form.

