| Blood collection         | Clinical protocol: Stroke Units at Austin Health, Eastern Health, Western Health, Epworth Camberwell, and Monash University: The Alfred Centre campus | As per respective inpatient clinical care needs | MRI                                                                              | Baseline; 4 months; 1 year                                                    | 1 per visit                                                                                                       |
|                          |                                                                                                                                                       |                                                 | Blood for APOE genotyping, BDNF, HbA1c, future genetic and blood marker analyses | Baseline (additional 10ml sample taken for genetic testing); 4 months; 1 year | 27ml for 2 month, 4 month and 1 year visit
Additional 10 ml (total=37ml) for 2 month, 4 month, or 1 year visit |
|                          |                                                                                                                                                       |                                                 | Cognitive and Mood Testing                                                       | Baseline; 4 months; 1 year                                                    | 1 set of tests per visit                                                                                          |
|                          |                                                                                                                                                       |                                                 | Home-based exercise intervention (both groups)                                   | Intervention starts at baseline and continues 3 times per week for 8          | 60 minutes per session                                                                                            |

|                                                                 | weeks                                                              |                                                                            |
|-----------------------------------------------------------------|--------------------------------------------------------------------|----------------------------------------------------------------------------|

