| Aerobic capacity test (VO 2 peak graded stress test) | Baseline; 4 months; 1 year                                         | 30-60 minutes total, dependent on individual capacity                      |
| Physical activity monitoring                                    | 1 week after each testing time-point                               | Actiwatch monitors worn for a duration of 1 week                           |
| Sleep monitoring                                                | 1 week after each testing time-point, as well as prior to Baseline | 7-day Sleep Diary and sleep questionnaire (completed at home)              |
| Dietary intake assessment                                       | 1 week after each testing time-point                               | 3-day food diary recorded with Research Food Diary app (completed at home) |
| Gut microbiome                                                  | Baseline; 4 months; 1 year                                         | 1 sample (completed at home)                                               |

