## **XI. Stool sample collection for microbiome analysis**

At each timepoint, participants will be provided with a specimen kit to take home and asked to collect a stool sample. They will be asked to store the sample in the freezer until it can be returned to the facility. Participants will also receive a thermo bag to place the sample in for preservation purposes when returning it to the facility. This will be completed after each timepoint. In the case of Visit 2 (2-month timepoint), participants will complete the stool sample before they begin the exercise intervention.

The samples will be used to determine the effects of exercise on gut microbiome composition, and relationships with cognitive and brain volume change after stroke.

A portion of samples from each participant will be transferred from The Florey or Sunshine Hospital (depending on site) to Monash University for analysis by A/[name] and her laboratory team who will prepare stool samples using reagents and arrange for microbial sequencing.

It is possible that unused portions of stool samples collected in the current study will be tested for other biological markers at some stage in the future. Any further analysis of stool samples not detailed in this Protocol will be raised with Austin Health HREC if/when that time arises.

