## **XII. Dietary intake monitoring**

Dietary intake will be recorded by participants using the Research Food Diary app (Xyris Software (Australia) Pty Ltd.) At the 2 month timepoint, participants who have a smart phone (Android or iOS) will receive information on the app's basic functions and how to record dietary intake on the app. Participants will complete a 3-day food diary (2-week days and 1 weekend) in the week following each timepoint: 2 months, 4 months, and 12 months. At each timepoint, participants will use the feature "share" in the app to send their 3-day food diary to the study nutritionist, who will check the food diary for completion. If any inconsistency is observed, the nutritionist will advise the Project Coordinator, who will contact the participant by phone, and corrections will be performed if necessary. Nutrient analysis will be undertaken using an Australian food composition database, the FoodWorks Professional (v8) software.

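### Nothing requires the 2-month actigraphy week and food diary to finish before allocation or the first exercise session, so baseline activity, objective sleep and diet may be recorded under treatment

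*Protocol*

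**What the plan says.** **Allocation and start of treatment.** Protocol 5.c states: "After the first time-point assessments, participants will be randomly allocated into one of two exercise groups". Section 5.a (Timelines and feasibility) states: "The 8 week intervention will commence at 2 months after stroke". The schedule table in 5.b has "Intervention starts at baseline and continues 3 times per week for 8" weeks. The glossary treats the baseline assessment and delivery of the intervention as one time point.

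**Activity.** In 5.d.IX the Actiwatch is "fitted onto participants at each of the three timepoints throughout the study, after the MRI scan and cognitive testing has been completed" and is worn around the clock for 7 days. The 5.b table likewise places activity monitoring in the week after each testing time point.

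**Diet.** In 5.d.XII the 3-day food diary is kept "in the week following each timepoint: 2 months, 4 months, and 12 months". Section 5.a adds that it comes after the stool sample.

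**Sleep.** The 5.b table lists the sleep diary and questionnaire "1 week after each testing time-point, as well as prior to Baseline". Section 5.d.X ties the diary to the Actiwatch week at the same three time points and mentions no additional week.

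**Stool.** Here alone there is an ordering rule for the 2-month visit (5.d.XI): "participants will complete the stool sample before they begin the exercise intervention".

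**Home visit.** Section 5.a provides that "One home visit will take place 1-week prior to the initial baseline assessment".

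**The concern.** A baseline value should be fixed before the participant knows the allocation and before treatment can act on it. The 2-month recordings of activity, objective sleep and diet all start after the visit whose assessments precede randomisation, and no rule makes randomisation or the first session wait for them. The ordering rule for the stool sample shows that the authors recognised the issue for one measure and did not extend it to the others. Participants know their group from the programme they receive (5.c).

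Sleep and dietary intake are listed secondary outcomes (4.c). Change in sleep is a planned moderator (5.d.X), and sleep is a candidate mediator in the exploratory analyses (8.c.iii). Section 5.d.IX also makes time spent active a covariate for data analysis, without naming the time point or the models. If the baseline week already contains part of the treatment, a change from baseline or a baseline-adjusted contrast no longer measures the whole effect. A covariate recorded after allocation may itself be affected by allocation.

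**Working it through.** The plan gives no figure on this point, so the check is a comparison of the schedule statements followed by calendar and dose arithmetic.

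**1. Order of events at 2 months**

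| Event | Timing given | Must precede allocation or exercise? |
|---|---|---|
| MRI, cognitive tests | 2-month visit | Yes, as part of the assessments before randomisation (5.c) |
| Stool sample | At home after the visit | Yes, before exercise (5.d.XI) |
| Actiwatch, 7 days | From after MRI and cognitive tests (5.d.IX) | No rule |
| Sleep diary | Actiwatch week (5.d.X); also before baseline (5.b table) | The two sections disagree |
| Food diary, 3 days | Week after the visit, following the stool sample (5.a, 5.d.XII) | No rule |
| Exercise programme | Starts at baseline, 3 sessions a week (5.b table) | Not applicable |

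The interval from assessment to randomisation, and from randomisation to session 1, is not stated.

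**2. Does the calendar settle it?** Assume a month of 365.25/12 = 30.44 days.
- From 2 to 4 months post-stroke: 2 × 30.44 = 60.9 days.
- Programme: 8 × 7 = 56 days, leaving 60.9 − 56 = 4.9 days.
- A 7-day recording followed by the full programme: 7 + 56 = 63 days, which is 63 − 60.9 = 2.1 days more than the nominal interval.

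A full recording week before session 1 therefore does not quite fit the nominal timetable. However, baseline is only approximately 2 months post-stroke (glossary), so the calendar neither forces nor excludes overlap.

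**3. Exercise in the recording week if overlap is full.** Inputs are three 60-minute sessions a week (5.b), and 30 minutes of aerobic activity per fitness session against none in the balance programme (exercise table, 5.b).
- Supervised exercise, either arm: 3 × 60 = 180 min, or 180/7 = 25.7 min/day. This is 180/(7 × 24 × 60) = 1.8% of the recorded week.
- Aerobic work, fitness arm: 3 × 30 = 90 min, or 90/7 = 12.9 min/day. Balance arm: 0.

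The supervised time is equal in the two arms but its content is not, so any effect on the baseline may differ by arm. The 4-month recording week follows the nominal end of the programme and would not contain these sessions.

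**4. Can the bias be sized?** If a fraction f of the eventual effect is already present in the baseline week, a change score loses the fraction f of it. A baseline-adjusted contrast with baseline slope b loses f × b. The protocol gives neither f nor b for sleep or diet, so no percentage can be stated.

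**The case against.** A reader might infer that the baseline week is scheduled inside exercise week 1. The protocol does not say that, and no section dates session 1. Several steps come between the scan and the first session: randomisation is stratified by baseline total brain volume (5.c), so the scan must first be measured; the equipment pack is delivered after the assessment (5.b); and a physician must clear the participant (7.a). Collecting the stool at home before exercise also presupposes some gap. Section 5.a speaks loosely of recording activity around the visits and lists Actiwatch fitting among the 2-month activities, so the home week might be read as part of the assessments that precede randomisation. The timeline figure is not available here and may show the order. All of this stands, and it limits the point to what the text permits.

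Other pre-treatment information exists. The 5.b table has a sleep diary and questionnaire before baseline, the PSQI looks back one month (5.d.X), and the PASE is given in person at 2 months (5.d.VII). These soften the loss for self-reported sleep and activity. They do not supply a protected baseline for actigraphic sleep and activity or for the food diary, and the pre-baseline sleep entry is absent from 5.d.X.

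A reader might also infer that the primary result is biased. It is not on the stated model: the ANCOVA in 8.c.i adjusts for baseline brain volume and mRS. It would be touched only if the activity covariate of 5.d.IX entered it with a value recorded after allocation. Finally, hypothesis iii and aim 3 concern associations, and no baseline-adjusted between-arm model for sleep or diet is written out, so the harm depends on analyses still to be specified.

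**Conclusion.** The point holds as a gap in the schedule. The written order lets a site record baseline activity, objective sleep and diet after allocation and during exercise week 1, and nothing prevents it. It does not hold as a statement that this will happen. If overlap is full, the baseline week contains up to 180 min of supervised exercise per arm, with 90 min of aerobic work in the fitness arm only; this assumes that all three week-1 sessions fall within the 7 days. The analyses at risk are change or baseline-adjusted analyses of the secondary sleep and diet outcomes, the use of sleep change as a moderator, and any model that uses time spent active from that week. The primary ANCOVA as written is not at risk. The size of any bias is unknown, since any attenuation percentage would rest on invented inputs. The matter still deserves correction, because the data collection schedule creates it and later analysis cannot restore a baseline that was recorded under treatment.

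**What to change.** 1. In 5.b, 5.d.IX and 5.d.X, require the baseline 7-day Actiwatch recording and sleep diary to be complete before randomisation. Issue them at the home visit already planned one week before baseline, and remove the watch for the MRI.
2. In 5.d.XII and the 5.b table, require the baseline 3-day food diary to be complete before allocation is disclosed and before the first exercise session. Either keep it after the stool sample, as 5.a orders, or amend that order explicitly.
3. Reconcile the pre-baseline sleep entry in the 5.b table with 5.d.X, so that both describe the same recording weeks.
4. Leave the 4- and 12-month recording weeks as they are.

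The cost is protocol wording and handing out devices at an existing visit. Some devices will go to people who then fail baseline tests, and session 1 may wait a few days for the food diary.
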